## Methods

### Study design and ethical considerations

“The Up Project” comprises a quasi-experimental study in which the sample will be selected through cluster sampling, with workplaces serving as the basis for establishing both interventions and control groups (ClinicalTrials.gov identifier: NCT05844267). This project has been approved by the Ethics Committee of Pontificia Universidad Católica de Valparaíso (BIOEPUCV-HB 580–2023) and will be conducted following the Declaration of Helsinki and the guidelines of the SPIRITS (Standard Protocol Items: Recommendations for Intervention Trials) checklist (39). Additional information is provided in the Supplementary material. Written consent will be obtained from the participants before beginning and will be guarded and stored by the principal investigators ([name] and CB) to maintain the confidentiality of the participants. All protocol modifications will be communicated and registered on ClinicalTrials.gov.

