### Sample recruitment

Desk-based workers (60 in total) will be recruited voluntarily from universities and educational institutes in the Valparaiso region, Chile. We will extend an open invitation to all desk-based workers of the Pontificia Universidad Católica de Valparaíso (PUCV) in the Faculty of Philosophy and Education and the central office located in the Central Campus. The control group sample will be obtained from Naval Academy’s desk-based workers. It is important to note that the participants of the control group are civilians or retired marines who do not undergo any type of military training or physical tests. Subsequently, our research team will be visiting their offices to conduct face-to-face recruitment. During this process, the participants will be provided a detailed description of the scientific background, research objectives, and safety measures by our research group. We aim to ensure that all participants clearly understand our research and feel comfortable participating in our study. Once accepted, they will be assigned to a group according to the work site. Upon completion of the study, the participants will be given a full report on changes in body composition, physical activity levels, and sedentary time. After the data collection period, the control group will have the opportunity to participate in the same intervention program.

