#### Sample size calculation

The sample size was calculated using the G*Power software. This calculation considered the repeated measures of factorial analysis of variance (ANOVA), with an effect size (f) of 0.20, alpha value of 0.05, and beta of 0.80. The study involved three groups and two evaluation time points (pre/post), with an estimated follow-up loss of 10%. Consequently, 60 participants will be distributed as 20 participants per group: two experimental groups (B-B led by professionals and unled C-P) and one control group. The groups will be sex balanced because of the predominance of women in this type of work. In this sense, for selecting participants, we used the sex ratio of workers in group B-B (the lowest men proportion). In this site, there is a proportion of 27.1% of men and 72.9% of women; thus, our sample will try to approach this proportion in the two remaining groups.

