To prevent participant dropout and maintain motivation throughout the intervention, both variations and combinations of the main muscle groups to be worked on will be introduced. The two muscle groups will be combined daily, with 70% of the time allocated to the first group and 30% to the second group. The order and time percentages will be reversed the following week. In the second month, elastic bands and canes will be incorporated to support the exercise performance. The main work session will last nearly 12 min.

It is important to note that although B-B includes exercises that differ from those of the application, the intensity will be the same. Borg’s scale will be employed for this purpose to ensure comparability between the interventions. In this sense, our investigation group conducted a pilot test of the selected exercises to determine the correct intensity in relation to the exercises proposed by the application. In addition, the staff in charge of conducting the group B-B active breaks ensured that the sessions were performed between light and moderate intensity (i.e., RPE 3–4). Participants played an indirect role in the validation of the intervention’s B-B component. Although no focus group was conducted to directly gather their input for the intervention’s design, which is based on government programs, their well-being at work was taken into account when creating the exercise plans (for instance, the subjects did not wish to perspire, so the exercises were of mild to moderate intensity). Furthermore, it should be emphasized that the participants in both intervention groups are affiliated with the institution where the principal investigators are employed, thus providing a known context for the participants.

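### Intervention versus control coincides with institution, yet the plan sizes and analyses the 60 workers as independent and relies on propensity analysis for causal conclusions

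*Protocol article*

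**What the plan says.** Under Study design and ethical considerations, the protocol article calls the study quasi-experimental and says that "the sample will be selected through cluster sampling, with workplaces serving as the basis for establishing both interventions and control groups". Sample recruitment gives the rule for each worker: "Once accepted, they will be assigned to a group according to the work site". The same section invites university staff "in the Faculty of Philosophy and Education and the central office located in the Central Campus", and adds: "The control group sample will be obtained from Naval Academy’s desk-based workers". The Booster breaks section confirms that "the participants in both intervention groups are affiliated with the institution where the principal investigators are employed". Sample size calculation describes the booster-break (B-B) location in the singular: "In this site, there is a proportion of 27.1% of men and 72.9% of women".

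The sample size is a G*Power repeated-measures ANOVA on individuals: effect size f 0.20, alpha 0.05, three groups, two time points and 10% loss, giving 20 per group. No ICC or design effect appears.

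The Data analysis plan specifies propensity analysis for the primary outcomes plus ANOVA or ANCOVA. The covariates it names are all properties of individuals (sex, age, socioeconomic status, eating and smoking habits). It says that propensity analysis makes the groups comparable on influential variables whether or not they are known. Clustering is mentioned there only to explain why allocation could not be concealed. The limitations in the Discussion admit the lack of randomisation, but not the overlap of arm with workplace.

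**The concern.** Every control worker belongs to one institution and every intervention worker to another. Anything that moves outcomes at one of them during the 12 weeks, such as workload, local term schedule, management or familiarity with the investigators, enters the intervention-versus-control estimate and cannot be told apart from the programme. Self-reported stress and occupational pain, both principal outcomes, look particularly exposed.

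Precision is affected too. ANOVA and ANCOVA on individuals judge arm differences against variation between people within a site. If workplaces also differ in how their staff change over time, that variation is missing from the standard error, so intervals are too narrow.

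The Background sets out to establish the efficacy of the two programmes, and the Discussion looks ahead to government and company programmes. The design supports a weaker statement than that.

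**Working it through.** **Step 1. Reproduce the planned 60.** Inputs from Sample size calculation: f = 0.20, alpha 0.05, power 0.80 (the article labels this value beta), k = 3 groups, m = 2 measurements, 10% loss. The pre/post correlation rho is not given, so it is assumed. The noncentrality for time and for group-by-time is λ = f²·N·m/(1 − rho).

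- Time effect, rho 0.5: N = 54, λ = 0.04 × 54 × 2 / 0.5 = 8.64, power 0.822.
- Group-by-time interaction, rho 0.6: N = 54, λ = 0.04 × 54 × 2 / 0.4 = 10.8, power 0.823.
- Both then give 54 / 0.90 = 60.

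Other settings tried do not give 60. For example, the interaction at rho 0.5 needs 66, or 74 with loss, and the between-groups effect needs at least 126 before loss. Every setting that returns 60 treats workers as independent, that is, with a design effect of 1.

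**Step 2. Count the workplaces.** Three locations are named: the faculty, the university's central office and the Naval Academy. There are three groups, and assignment is by work site. With one site per arm, degrees of freedom for site within arm are 3 sites − 3 arms = 0. Site variance cannot be estimated, and a random site effect cannot be separated from the arm effect.

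**Step 3. Consequence if the workplace ICC is positive.** Let n = 20 per site. Let ICC refer to the quantity analysed (change or baseline-adjusted outcome), and treat the three site effects as independent draws. Under the null:

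- design effect = 1 + (n − 1)·ICC
- ratio of true to estimated variance of an arm contrast, R = (1 + (n − 1)·ICC)/(1 − ICC)
- pairwise type I error = P(|t₃₈| > t_crit/√R)
- three-group type I error = P(F₂,₅₇ > F_crit/R)

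| Assumed ICC | Design effect | R | Effective n per arm | Pairwise type I | F-test type I | F test, simulated |
|---|---|---|---|---|---|---|
| 0 | 1.00 | 1.00 | 20.0 | 5.0% | 5.0% | 5.0% |
| 0.01 | 1.19 | 1.19/0.99 = 1.20 | 16.8 | 7.3% | 8.1% | 8.0% |
| 0.02 | 1.38 | 1.38/0.98 = 1.41 | 14.5 | 9.6% | 11.5% | 11.4% |
| 0.05 | 1.95 | 1.95/0.95 = 2.05 | 10.3 | 16.6% | 22.3% | 22.4% |
| 0.10 | 2.90 | 2.90/0.90 = 3.22 | 6.9 | 26.6% | 38.1% | 38.5% |

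The simulation used 40,000 replicates per ICC. With 18 per arm after 10% loss, the picture barely changes: pairwise 7.0, 9.1, 15.4 and 24.9%; F test 7.8, 10.8, 20.6 and 35.4%.

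**Step 4. Would more workers help?** Effective n per arm is n/(1 + (n − 1)·ICC), which tends to 1/ICC as n grows. The ceiling is 20 at ICC 0.05 and 10 at ICC 0.10, however many workers are recruited at the same sites.

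**Step 5. Does the propensity analysis help?** It balances the measured individual covariates put into the model. Institution determines whether a worker is in an intervention or the control group, so it has no overlap between the two and cannot be balanced. Unmeasured variables are balanced only as far as they follow the measured ones.

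**The case against.** The article is open about much of this. It calls itself quasi-experimental, names clustering, lists non-randomisation as a limitation, discloses that both intervention groups share the investigators' institution, and plans covariates chosen with causal diagrams. All participants are measured on the same dates, which removes calendar effects common to everyone. Stable differences between sites, such as staff mix, largely cancel in change scores, so the relevant ICC may be small. All of this stands, and it is why the table is illustrative. None of it separates arm from workplace or removes events specific to one site.

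A second objection is that the three workplaces could be regarded as fixed rather than as a sample. Standard errors conditional on those sites are then not wrong for this reason. That also stands, but it turns the problem from understated variance into confounding of unknown size. The estimate is then the programme effect plus the workplace difference.

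A reader might also infer more than the text supports:

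- That the article states one workplace per arm. It does not say which university location hosts the computer-prompts (C-P) arm, so this is a strong inference. Only the separation of control from both interventions by institution is explicit.
- That type I error exceeds 5% whatever the data. This needs a positive ICC for the analysed outcome, and none is given.
- That a design effect in the sample size would have repaired matters. Step 4 shows it would not.
- That the B-B sub-groups of 4–5 need a random effect. The article does not say that membership is fixed, so few groups in one arm would be poorly estimated, and such structure is commonly left to an analysis plan.

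**Conclusion.** The concern holds in a conditional form. From the text alone, intervention versus control is aliased with institution, and neither the planned ANOVA/ANCOVA nor the propensity analysis can undo that. The statement that propensity analysis balances unknown variables is wrong. By strong inference, each arm is also a single workplace, so the B-B versus C-P comparison has the same weakness.

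The direction of the effect on the tests is firm: any positive workplace ICC on the change or adjusted outcome makes a nominal 5% test anti-conservative. The size depends on the ICC. Over an assumed 0.01 to 0.10, with 20 per site, type I error runs from about 7 to 27% for a pairwise test and about 8 to 38% for the three-group F test. The documents support no particular value in that range.

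This is not a detail that an unseen analysis plan could settle, because the layout leaves nothing from which to estimate site variation. As designed, the study can show that workplaces with and without a programme differed. It cannot by itself establish efficacy.

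**What to change.** 1. State under study design, data analysis plan and limitations that arm is aliased with workplace, and say which location hosts each arm.
2. Delete the claim that propensity analysis balances unknown variables. Say that it addresses measured individual covariates only.
3. Word the aims and conclusions as differences between workplaces that did and did not receive the programme, not as established efficacy.
4. Report each primary contrast with its naive confidence interval and with intervals inflated over an ICC range fixed in advance. For 0.01, 0.02, 0.05 and 0.10 with 20 per site, the width is multiplied by √R = 1.10, 1.19, 1.43 and 1.80. Label this a sensitivity analysis, because the ICC cannot be estimated here and the upper end of the range is a judgement.

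The cost is some rewording and a short calculation. The price is wider intervals and a weaker claim. Assigning B-B or C-P by office within the university is not recommended as the remedy: control would still sit at one outside institution, so the primary contrast would stay aliased, and neighbouring offices could contaminate each other.

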### Training of personnel and quality control

Our research group will organize training sessions for investigators and key personnel prior to data collection. Quality control and rigorous standardization of measurement protocols across centers are critical for the success of intervention studies (40). All investigators from our research group shared responsibility for quality control. The principal investigators will oversee regulatory compliance, protocol adherence, data accuracy, personnel training, and regulatory document management. During data entry, key variables will be checked for accuracy with assigned interval controls. A review will be required for any data entered outside the preset ranges. The principal investigators ([name] and CB) make the final decision to terminate the trial.

### Sample recruitment

Desk-based workers (60 in total) will be recruited voluntarily from universities and educational institutes in the Valparaiso region, Chile. We will extend an open invitation to all desk-based workers of the Pontificia Universidad Católica de Valparaíso (PUCV) in the Faculty of Philosophy and Education and the central office located in the Central Campus. The control group sample will be obtained from Naval Academy’s desk-based workers. It is important to note that the participants of the control group are civilians or retired marines who do not undergo any type of military training or physical tests. Subsequently, our research team will be visiting their offices to conduct face-to-face recruitment. During this process, the participants will be provided a detailed description of the scientific background, research objectives, and safety measures by our research group. We aim to ensure that all participants clearly understand our research and feel comfortable participating in our study. Once accepted, they will be assigned to a group according to the work site. Upon completion of the study, the participants will be given a full report on changes in body composition, physical activity levels, and sedentary time. After the data collection period, the control group will have the opportunity to participate in the same intervention program.

#### Inclusion and exclusion criteria

In this study, participants will need to be desk-based women and men workers in order to be included, between 18 and 60 years of age, who belong to an educational institution in the Valparaiso region, with a full-time contract.

As exclusion criteria will be considered participants who do not have a full-time job, individuals with physical limitations for physical exercise or undergoing weight loss treatment, pregnant and lactating (in the first 6 months postpartum) women (41), or pacemaker users (42). In addition, participants with a participation frequency lower than 70% in the protocol will not be considered; however, a sensitivity analysis will be performed based on the intention-to-treat principle (43).

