#### Control group

The control group will not have any type of intervention; they will be asked to continue with their normal life habits. At the end of the study, participants will be invited to participate in a physical activity program at their workplace.

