#### Follow up of participants

For the C-P group, the computer application will record the number of times the breaks will be accepted, rejected, or postponed, and it will generate a weekly summary. Furthermore, a member of our research group will consistently make phone calls to ensure that everything remains in order. In the case of the B-B group, all sessions will be recorded, with attendance tracking for all participants. Meanwhile, for the control group, a research group member will periodically remind them of the recommendations provided at the beginning of the 12 weeks. After the intervention, participants will be compensated by receiving a report with the values provided by accelerometry and a complete report of their body composition from the DXA measurements. There will be no monetary compensation. In addition, to qualitatively analyze the participants’ experience with the interventions, general and specific questions will be asked about the performance of the breaks (C-P and B-B). These questions will be asked in a private questionnaire format so as not to influence the answers of the participants. These results will be analyzed as a secondary objective in order to identify barriers and facilitators to be considered in future studies. For more information on these questions consult Supplementary material.

In case of desertion for any reason (i.e., leaving the country, change of job, impossibility of measurements), a sensitivity analysis will be performed with and without intention to treat. It is important to note that the exercise protocol was based on previous recommendations by Chilean governmental organizations, and that the protocol is designed to pose little or no risk to the health of the participants. However, in case of any type of injury risk, the participants’ institutions have medical insurance that will be effective if necessary.

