In parallel, sensitivity analyses will be performed according to the intention-to-treat principle. All analysis models will also adjust for relevant covariates such as sex, age, socioeconomic status, eating habits, smoking habits among others depending on their relevance in the model studied. To determine which variables are appropriate to use as covariates, directed acyclic graphs will be explored. These graphs are built on the expert knowledge of the researcher, which would facilitate the causal understanding of the phenomenon and the type of linkage between the variables involved, minimizing the introduction of bias during the design of the study and in the analysis of results (80, 81). All analyses will be performed in different software according to the needs of the researchers (e.g., R Studio, Jamovi, SPSS).

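### The main analysis drops participants below 70% participation, a filter that in practice reaches only the two intervention arms, while intention-to-treat is left as a sensitivity analysis

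*Protocol article*

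**What the plan says.** Under Inclusion and exclusion criteria, next to conditions that can be checked at enrolment, the Protocol article adds that "participants with a participation frequency lower than 70% in the protocol will not be considered; however, a sensitivity analysis will be performed". The sentence ends by basing that sensitivity analysis on the intention-to-treat principle.

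The Data analysis plan gives intention-to-treat the same place: "In parallel, sensitivity analyses will be performed according to the intention-to-treat principle". Follow up of participants says that, for people who leave the study, "a sensitivity analysis will be performed with and without intention to treat". No section makes intention-to-treat the main analysis.

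On the comparator, the Control group section says: "The control group will not have any type of intervention; they will be asked to continue with their normal life habits". Follow up of participants describes an application log of breaks for the computer-prompt arm and attendance tracking for the booster-break arm. For controls it describes only periodic reminders of the initial recommendations.

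The Background gives the primary hypothesis: both interventions will do better than control, with no difference expected between the two.

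**The concern.** An exclusion criterion should be something that can be applied before follow-up begins. Participation below 70% is behaviour during the 12 weeks. Using it to decide who is analysed makes the main analysis per-protocol, although the article does not call it that.

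The difficulty is greater here because the filter is one-sided. A control has no session to miss and no prompt to reject. Control workers who would have been poor attenders stay in, while their counterparts in the intervention arms are taken out. People who keep attending may differ in motivation, activity, stress or health from those who do not, whatever the breaks themselves achieve. Several of the outcomes (physical activity, sedentary time, perceived stress) are of the kind that could follow such differences. The contrast affected is the one in the primary hypothesis.

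**Working it through.** **Step 1. Who can be filtered?**

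| Arm | Intervention received | Participation record described | Can fall below 70%? |
|---|---|---|---|
| Booster breaks | Led session each working day | Attendance | Yes |
| Computer prompts | 2-minute breaks every hour over 8 hours | Breaks accepted, rejected or postponed | Yes |
| Control | None | None described | No, as written |

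**Step 2. Which analysis is the main one?** The article does not label a primary analysis set. The exclusion sentence removes low participators, and both that sentence and the Data analysis plan call intention-to-treat a sensitivity analysis. What remains as the main analysis is the set with at least 70% participation.

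**Step 3. How large could the bias be?** The plan has no figure of its own to reproduce on this point. It gives neither the share who will fall below 70% nor the relation of adherence to outcome, so both are assumed here:

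- q = share of each intervention arm excluded, taken as the least adherent (10, 20, 30%)
- r = correlation between adherence and change in outcome that would exist with no treatment effect (0.3, 0.5)
- adherence and change are bivariate normal, and no control is excluded

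With no true effect, the mean change among those kept in an intervention arm exceeds the mean of the unselected controls by

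bias = r × φ(z_q) / (1 − q), in SD of change,

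where z_q is the q-quantile of the standard normal and φ its density.

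| q | φ(z_q) | φ(z_q)/(1 − q) | Bias, r = 0.3 | Bias, r = 0.5 |
|---|---|---|---|---|
| 10% | 0.1755 | 0.195 | 0.06 | 0.10 |
| 20% | 0.2800 | 0.350 | 0.11 (0.105) | 0.18 (0.175) |
| 30% | 0.3477 | 0.497 | 0.15 | 0.25 |

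With r = 0 the bias is zero for every q.

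**Step 4. What does that do to the test?** A simulation used 20 per arm, no true effect, the same filter on the two intervention arms only, a three-group F test on change at a nominal 0.05, and 5,000 runs per setting. The rejection rates were:

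| q | r = 0 | r = 0.3 | r = 0.5 |
|---|---|---|---|
| 10% | 0.050 | 0.056 | 0.055 |
| 20% | 0.047 | 0.063 | 0.081 |
| 30% | 0.053 | 0.070 | 0.103 |

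The inflation is small when few are excluded. It reaches about twice the nominal level at the upper end of these assumptions.

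**The case against.** The strongest reply is that the trial is not randomised. Groups are formed by work site and controls come from a different institution, so intention-to-treat has no randomised comparison to protect, and site confounding remains under either analysis. That is true. The 70% rule nevertheless adds a second, avoidable selection after baseline.

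Next, the Data analysis plan provides for propensity analysis and for covariates chosen with directed acyclic graphs. These may reduce the selection where measured baseline variables predict adherence. They cannot be relied on to remove it, because controls who would not have adhered cannot be identified. The article's statement that propensity analysis balances unknown as well as known variables does not supply the missing protection.

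Third, intention-to-treat results are promised anyway, so readers should see both. That also stands, and it limits the harm. But if the two disagree, the plan has already named which one is the main result.

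Some stronger readings are tempting but not supported:

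- **The bias is established, in size or direction.** Every value of q and r above is assumed. Favouring the interventions is the likely direction, not a demonstrated one.
- **The rule costs power, so intention-to-treat would gain it.** Take f = 0.20, an assumed pre/post correlation of 0.5 and 18 per arm, so that the adherers' effect is about 0.85 SD of change in both intervention arms. Power is then 73%. Excluding 10/20/30% leaves 16/14/13 per intervention arm and power of 71/68/66%. If those excluded gain nothing, keeping them dilutes the effect to 0.85 × (1 − q) = 0.765/0.68/0.595 SD, and power is 63/52/42%. The case for intention-to-treat is validity, not power.
- **The 10% loss allowance in the sample size leaves these exclusions uncovered.** The article does not say what counts towards the 10%, and people who leave the study may be largely the same people who fall below 70%.
- **The threshold is a different filter in the two active arms.** The article says what is logged but not how participation frequency is calculated for computer prompts. That definition may sit in the full protocol.
- **The imputation wording is part of the same fault.** It is a separate matter, commonly left to the statistical analysis plan.

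**Conclusion.** The point holds. As written, the main analysis excludes people for behaviour after the intervention has started, the exclusion can in practice reach only the two intervention arms, and the analysis without that exclusion is given a supporting role. This adds a plausible bias to the primary contrast with control, probably in favour of the interventions and over and above work-site confounding.

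Its size is unknown. The range of about 0.06 to 0.25 SD of change rests on the assumed r of 0.3 to 0.5 and q of 10 to 30%, and the bias vanishes if adherence is unrelated to change. The conclusion rests on the analysis-set rule and not on any of these figures.

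**What to change.** Three changes of wording:

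1. Delete the 70% participation sentence from Inclusion and exclusion criteria.
2. State in the Data analysis plan that the primary analysis includes all enrolled participants, grouped by work site, whatever their participation. Keep the planned propensity and covariate adjustment, which addresses site confounding.
3. Keep the at-least-70% set as a sensitivity analysis labelled per-protocol, and note that the threshold cannot be applied to controls. Align the sentence on leavers in Follow up of participants with this.

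Both analyses are already planned, so the change is to which one is primary and needs no additional participants. The cost is a primary estimate that may be smaller, with lower power against the effect expected among adherers, because non-adherers dilute it.
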